### Study outcome

The study outcome will be the decrease in oral *Candida* carriage defined by *Candida* spp. colony forming unit (CFU) counts, originating from both denture biofilm and palatal mucosa.

### Explanatory variables

Data on a series of potential confounders and/or modifiers of study outcome will be collected. These will include baseline data on the following.

#### Sociodemographic and medical variables

Age, sex, ethnicity, education, medical history, medication profile, and smoking habits will be assessed at baseline.

#### Oral health and denture-associated variables

The baseline data will include dental history, years of edentulism, history of tooth loss, age of the maxillary dentures, and oral hygiene/denture hygiene habits (cleaning frequency, nocturnal wear, and mouthwash use), as well as satisfaction with oral health and existing dental prostheses. Denture cleanliness will be evaluated using the modified Hoad-Reddick classification [44, 45]. A clinical assessment of vertical dimension of occlusion, stability, and retention of the maxillary prosthesis, as well as shape and resiliency of the maxillary edentulous ridge, will be carried out according to standard prosthodontic criteria [44].

The data on oral hygiene/denture hygiene habits and denture cleanliness will be collected at each follow-up to create a time-dependent hygiene variable.

### Data collection

Data collection will be conducted using a self-administered questionnaire and a clinical examination conducted by trained and calibrated dentists using a front surface mirror and probe (XP23/QW; Hu-Friedy, Chicago, IL, USA). Photographs of the palate will be taken with a Nikon D90 camera (105 mm f/2.8 D, macro flash SB-21; Nikon Co., Tokyo, Japan). These photographs will be used to obtain a diagnostic consensus from research team members.

To facilitate conducting the study, baseline data will be collected at the participant’s first visit to the research center, following informed consent. However, if the candidates need more time to reflect on their participation and commitment to the study, another visit will be scheduled for baseline assessment. Follow-up data collection will be conducted at 3 and 6 months post randomization by the same examiner at each research center. The data collection sessions are estimated to last approximately 45–60 minutes.

### Biological sample collection and analysis

Collection of denture biofilm will be performed following the standardized sonication technique protocol [44, 46, 47]. Palatal biofilm will be collected using a sterile swab on the central palatal mucosa (1 cm^2^) [48], placed in a sterile tube with 5 ml saline, and sonicated for 2 minutes. In order to standardize the collection time, samples will be collected between 9 a.m. and 12 p.m. The biological samples will be immediately transferred to the microbiological laboratory at each center.

Swabs and sonicates will be mixed separately with saline, diluted according to the defined protocol [44], inoculated on Sabouraud-Dextrose 4% agar for *Candida* spp., and incubated at 37 °C for 48 hours. Identification of different *Candida* species will be confirmed by growth on selective culture medium (CHROMagar Candida, Paris, France). CFUs will be counted and expressed as CFU/ml, after correction for volume and dilution factor.

### Sample size

Sample size estimation assumes the minimal clinically important between-group difference in the *Candida* CFU/ml mean change score to be 30,000, with a standard deviation of the distribution of the change score of 31.6 (based on estimates from our pilot data) [41]. These parameters lead to a total sample size of 52 participants (26 for each study arm) to ensure a power of 85% for rejecting the null hypothesis with a conservative dropout rate of 10%.

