### Statistical analysis

Data entry and analysis will be conducted in a blinded fashion. An interim analysis has not been planned due to the low frequency of adverse effects observed during the pilot trial [41]. Basic descriptive statistical analyses will be performed for all variables after being tested for normality.

Bivariate analysis, as well as mixed-model analyses for repeated measures, with time and intervention as independent variables, will be conducted following testing for normality. In the case of non-normal distribution, the Brunner Langer nonparametric test will be used.

All analysis will be performed in adherence to the intention-to-treat principle [49]. *p* ≤ 0.05 will be considered statistically significant. All analysis will be performed using SPSS version 24 and SAS 9.4 for Windows.

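### The sample-size inputs are printed on scales about 1,000-fold apart; on a common scale they give 46 to 48 participants, not 52, a discrepancy in the conservative direction

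*Protocol article*

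**What the plan says.** The Sample size section of the protocol article bases the calculation on the "minimal clinically important between-group difference in the" mean change score for Candida CFU/ml. It takes this difference "to be 30,000, with a standard deviation of the distribution of the change score of 31.6 (based on estimates from our pilot data". The SD carries no unit and no scale factor.

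From these figures alone the section derives "a total sample size of 52 participants (26 for each study arm"). The target power is 85%, and the dropout allowance of 10% is described as conservative.

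The section gives no significance level. The Statistical analysis section does: p "≤ 0.05 will be considered statistically significant". Sidedness is not stated. The section on biological samples reports counts as CFU/ml, and the article mentions no logarithmic or other transformation. A nonparametric test is named in the Statistical analysis section, but only as a fallback if the data are not normal.

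**The concern.** A difference and the SD of the same change score must be in the same unit. Here one is 30,000 CFU/ml and the other is 31.6, so at least one of them is misprinted or expressed on another scale. The paragraph presents the sample size as the direct result of these inputs, and it is the article's only justification of the trial's size.

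Two things are at stake. A reader cannot verify the calculation as printed. And because power depends strongly on the ratio of difference to SD, the stated power can be relied on only once the SD has been confirmed. The natural repair, reading the SD as thousands of CFU/ml, also fails to return 52 at 85% power, so correcting the unit alone would leave the paragraph inconsistent.

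**Working it through.** **Inputs.** Difference 30,000 CFU/ml, SD 31.6, power 85%, dropout 10%, 26 per arm (all from Sample size); alpha 0.05 (from Statistical analysis). Two-sided testing is assumed, and one-sided testing is also tried.

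**Formula.** n per arm = 2 (z_alpha + z_power)² (SD/difference)², checked against the noncentral-t calculation for a two-sample t-test. Dropout: n/(1 − 0.10).

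**1. Inputs as printed.** 30,000/31.6 = 949. The formula gives 2 × (1.960 + 1.036)² × (31.6/30,000)², far below one participant per arm, and two per arm already have power of essentially 100%. The plan's 52 is not reproduced.

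**2. Inputs on a common scale.** Take the SD as 31.6 thousand. Taking the difference as 30 gives the same result, since only the ratio matters: 30/31.6 = 0.949.

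- Normal formula: 2 × (1.960 + 1.036)² × (31.6/30)² = 19.92, so 20 per arm.
- t-test: 20.93, so 21 per arm.
- After dropout: 20/0.9 = 22.2, so 23 per arm (46 in total); 21/0.9 = 23.3, so 24 per arm (48 in total).
- Inflating by 1.1 instead of dividing by 0.9 gives 22 or 24 per arm.
- One-sided alpha 0.05: 16 or 17 per arm, 36 or 38 in total after dropout.

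None of these reaches 52. The excess over the two-sided result is 52 − 48 = 4 to 52 − 46 = 6 participants.

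**3. Power at the stated size, two-sided, SD 31,600.** 26 × 0.9 = 23.4, so 23 evaluable per arm.

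| Evaluable per arm | t-test | Normal |
|---|---|---|
| 23 | 88.3% | 89.6% |
| 26 (no dropout) | 91.9% | 92.8% |

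**4. SD at which 23 evaluable per arm would give exactly 85%.** About 33,200 (t-test) or 34,000 (normal), against 31,600.

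**5. Unstated conventions that would give 52.**

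- 85% power with a 15% add-on for a rank test: 19.92 × 1.15 = 22.9; 22.9/0.9 = 25.5, so 26 per arm.
- 85% power divided by 0.864, the minimum asymptotic relative efficiency of the rank test: 19.92/0.864 = 23.06; 23.06/0.9 = 25.6, so 26 per arm.
- 90% power, normal formula: 23.32/0.9 = 25.9, so 26 per arm. Rounding to 24 before the dropout step gives 27 per arm, 54 in total.

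The two rank-test results also depend on rounding only at the end: rounding 23.06 up to 24 first gives 27 per arm. The Sample size section mentions none of these conventions.

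**The case against.** The strongest defence is that 52 participants do secure 85% power if the SD is 31,600: the t-test power with 23 evaluable per arm is 88.3%. The discrepancy is then a margin of 4 to 6 participants in the safe direction. The analysis section names a nonparametric fallback, and one ordinary allowance for a rank test brings 85% power to 52. The slip in the SD is also easy to recognize as thousands. All of this stands, and it limits the consequence. It does not cure the text, because the article attributes 52 to the stated parameters alone and those parameters as printed cannot produce it.

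Three stronger readings are tempting, and the article does not support them:

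- **That the trial is underpowered.** On the common-scale reading it has more than the stated power. A shortfall would need a pilot SD above about 33,200, and nothing in the article points to one.
- **That 90% power was really intended.** This match depends on when one rounds, contradicts the stated 85%, and has no more textual support than a nonparametric allowance.
- **That power and alpha cannot be known.** Both are stated, in different sections. What is unclear is the unit of the SD, and sidedness is not given.

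**Conclusion.** The point holds as an error in the stated inputs together with a modest, conservative mismatch. The scale error is certain: the difference and the SD of the same score are about 1,000-fold apart, and 52 cannot follow from them. The mismatch that remains is conditional. It assumes an SD of 31,600 CFU/ml, a two-sided 0.05 level, a plain two-sample comparison and 10% dropout. Under these assumptions the stated parameters give 46 to 48 participants, and 52 gives about 88% power rather than 85%. The true SD cannot be checked, because the pilot data are not in the article.

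**What to change.** Correct the Sample size paragraph:

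1. Check the SD of the change score against the pilot data and state it in CFU/ml, on the same scale as the difference.
2. State the alpha of 0.05 in that paragraph and that it is two-sided.
3. Keep 52. If the SD is confirmed as 31,600, either restate the power as about 88% (t-test, 23 evaluable per arm after 10% dropout), or keep 85% and state the allowance, for example for a nonparametric test, that leads to 52.
4. If the pilot SD differs from 31,600, recompute the power at 52 and report that figure.

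The cost is one look at the pilot data and one rewritten paragraph. Enrolment and the planned analysis do not change.

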### Statistical analysis

Data entry and analysis will be conducted in a blinded fashion. An interim analysis has not been planned due to the low frequency of adverse effects observed during the pilot trial [41]. Basic descriptive statistical analyses will be performed for all variables after being tested for normality.

Bivariate analysis, as well as mixed-model analyses for repeated measures, with time and intervention as independent variables, will be conducted following testing for normality. In the case of non-normal distribution, the Brunner Langer nonparametric test will be used.

All analysis will be performed in adherence to the intention-to-treat principle [49]. *p* ≤ 0.05 will be considered statistically significant. All analysis will be performed using SPSS version 24 and SAS 9.4 for Windows.

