**Methods/design:**

A pragmatic, two-parallel-arm, multicenter RCT will be conducted in Canada, Brazil, and Chile. Fifty-two adult complete denture wearers presenting with moderate to severe DES will be allocated randomly to two groups: the Intervention arm will consist of palatal brushing and standard oral and denture hygiene measures, while the Control arm will include only standard oral and denture hygiene measures. The study outcome will be the oral *Candida* carriage. Participants will be assessed at baseline, and at 3 and 6 months post intervention. Descriptive, bivariate, and mixed models with repeated measures will be performed following the intention-to-treat principle.

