### Study hypothesis

Edentate individuals with DES using palatal brushing and standard oral hygiene measures after each meal over a period of 6 months will show a clinically meaningful lower level of oral *Candida* carriage when compared with those who use only standard oral hygiene measures.

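### The repeated-measures model names time and intervention but no interaction, baseline covariate or primary contrast, so no named term estimates the between-arm difference in change on which the trial is sized

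*Protocol article*

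**What the plan says.** The Statistical analysis section announces bivariate analyses and mixed models for repeated measures, the latter "with time and intervention as independent variables, will be conducted following testing for normality". The fallback is: "In the case of non-normal distribution, the Brunner Langer nonparametric test will be used". The section does not say whether the response is the raw count or the change from baseline, which visits enter as responses, or which effect is the test under either method.

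Four other places bear on what the model should deliver:

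- Abstract, Methods/design: "Participants will be assessed at baseline, and at 3 and 6 months post intervention".
- Study hypothesis: brushing "over a period of 6 months will show a clinically meaningful lower level of oral" *Candida* carriage than standard hygiene alone.
- Study outcome: "The study outcome will be the decrease in oral" *Candida* carriage, counted in CFU from denture biofilm and palatal mucosa. No time point is given.
- Sample size: a between-group difference in "CFU/ml mean change score to be 30,000", with a "standard deviation of the distribution of the change score of 31.6". No time point is given here either.

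Baseline CFU is not among the covariates listed under Explanatory variables.

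**The concern.** The outcome and the sample size concern a between-arm difference in change. With raw counts at three visits as the response, that quantity is an intervention-by-time effect. A model with time and intervention as main effects has no parameter for it: the intervention coefficient is the arm difference averaged over the visits. Randomisation follows the baseline assessment, so the baseline visit contributes an expected difference of zero.

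Other readings of the same clause are possible, and they give different answers from the same data. The coefficient reported as the trial's result could be a three-visit average, a two-visit average of change, or a difference at one visit. With 52 participants and one named outcome, leaving this open allows the choice to be made after the results are seen. The literal reading gives an estimate smaller than the quantity used for sizing.

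**Working it through.** **Inputs.** From Sample size: difference 30,000, SD of change printed as 31.6, 26 per arm, 85% power, 10% dropout. From Statistical analysis: significance level 0.05. Assumptions: SD read as 31,600, two-sided test, equal correlation ρ between any two visits, 26 × 0.9 ≈ 23 completers per arm. The article gives no ρ, so a range is shown. Figures below are in thousands of CFU/ml; power is by noncentral t.

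**The plan's own figure.** n per arm = 2(1.960 + 1.036)² × (31.6/30)² = 19.9, so 20 (21 with the t distribution). Dividing by 0.9 gives 23 or 24 per arm, a total of 46 or 48. The stated 52 is not reproduced. With the SD as printed (31.6 against 30,000) the formula gives 1 per arm. That is a separate matter and the present point does not depend on it. With 23 per arm, an unadjusted comparison of change at one follow-up visit has 88% power.

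**Reading A: raw CFU at all three visits, main effects only.**

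- Visit SD: σ = 31.6 / √(2(1 − ρ)).
- Expected coefficient: (0 + d₃ + d₆)/3. With d₃ = d₆ = 30 it is 20. With d₃ = 15 it is 15. With d₃ = 0 it is 10.
- SD of a participant's mean: σ√((1 + 2ρ)/3). The standard error of the arm difference is this times √(2/23).

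| ρ | σ | SD of mean | SE | Power, d₃ = 30 | Power, d₃ = 15 |
|---|---|---|---|---|---|
| 0.3 | 26.7 | 19.5 | 5.75 | 93% | 72% |
| 0.5 | 31.6 | 25.8 | 7.61 | 73% | 49% |
| 0.7 | 40.8 | 36.5 | 10.76 | 44% | 28% |

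The shrinkage of the estimate does not depend on ρ; the power does.

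**Reading B: change from baseline at 3 and 6 months, main effects only.**

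- Expected coefficient: (d₃ + d₆)/2, which is 30 with equal effects and 22.5 with d₃ = 15.
- Variance of the mean of the two changes: 1.5σ²(1 − ρ) = 0.75 × 31.6², so SD 27.4 at any ρ.
- Power: 95% for 30 and 78% for 22.5.

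There is no baseline dilution. Adjusting the same two-visit average for baseline would give variance 31.6²(1 + 2ρ)/4. That is (1 + 2ρ)/3 of the unadjusted variance: 0.53, 0.67 and 0.80 at ρ = 0.3, 0.5 and 0.7.

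**Alternative: 6-month contrast adjusted for baseline CFU.** The variance is σ²(1 − ρ²) = 31.6²(1 + ρ)/2, which is (1 + ρ)/2 of the change-score variance. The SD is 25.5, 27.4 and 29.1 at ρ = 0.3, 0.5 and 0.7. For a difference of 30, power is 97%, 95% and 93%, against 88% for unadjusted change. Under randomisation the adjusted contrast estimates the same between-arm difference in change, undiluted.

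**The case against.** A reader might infer more: that the model contains main effects only, includes baseline as a response, therefore fails to test a 6-month hypothesis, and has power well below 85%. The article does not support any of these as fact.

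- **Main effects only.** Naming the factors of a repeated-measures model is ordinary shorthand in a condensed article and does not exclude their interaction. The Brunner-Langer method ordinarily tests group-by-time, which suggests that the parametric model may have the same structure.
- **Baseline as a response.** This is not stated. The change wording in Study outcome and Sample size fits reading B, where the dilution vanishes.
- **The 6-month hypothesis.** The Study hypothesis speaks of a period of 6 months and does not fix the 6-month visit as the contrast. An average over 3 and 6 months is compatible with it.
- **Power.** Even under reading A, power is 93% at ρ = 0.3 with a full 3-month effect. The one-third shrinkage also assumes equal effects at both follow-ups. With 45 at 3 months and 30 at 6, the average is (0 + 45 + 30)/3 = 25, a shrinkage of one sixth.
- **Scope.** Bivariate analyses are also planned and could compare change directly, and a full analysis plan may specify the model further.

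All of this stands and limits the claim. It does not remove the point. The one description given lists its independent variables, and neither of the two named corresponds to the difference in change when raw counts are analysed. Nothing else in the article says which effect is tested, and an analysis plan that followed the clause as written would carry the fault forward. Analysing change without baseline adjustment is valid under randomisation, so that part concerns efficiency and not bias.

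**Conclusion.** The point holds in a limited form, with moderate severity. The model as described does not fix a term that estimates the between-arm difference in change. Taken literally on raw counts at all three visits, it would report 20,000 where the true difference is 30,000 at both follow-ups, and 15,000 if the 3-month effect is half. Whether power falls below 85% depends on a within-person correlation that the article does not give. On a change-score response the estimate is not diluted by baseline, and the remaining cost is precision. The power figures rest on the SD being 31,600, equal correlations and 23 completers per arm. They describe the linear model and do not carry over to the nonparametric fallback.

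**What to change.** Replace the clause with a full statement of the model:

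- Response: CFU at 3 and 6 months.
- Fixed effects: intervention, visit, intervention-by-visit, and baseline CFU from the same sampling site (denture or palate).
- Primary test: one between-arm contrast named in advance, reported with its 95% confidence interval. Six months is the natural choice given the Study hypothesis, but the article does not fix it, so the investigators must state it. The 3-month contrast is then secondary.
- Fallback: if Brunner-Langer is used with baseline as a time point, the test is the group-by-time effect.

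If an interaction or a change-score response was always intended, saying so removes the dilution question, and adding baseline CFU still gains precision. The cost is analysis wording only. A baseline assessment already takes place, and no extra participants or visits are needed.

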### Data management, monitoring, and auditing

All data collected and entered at each center will be periodically checked by a data monitoring committee composed of two independent researchers and one end-user representative. Additionally, an independent audit could be conducted by the ethics committee of each center at any time.

### Risks, participant safety, and trial adherence

In the pilot phase of this study it was observed that for some participants palatal brushing caused minor discomfort; specifically, mild pain and minor bleeding of the mucosa occurred in 40% of the 48 study participants in the first few days [41]. However, all participants were able to adhere to the study protocol and instructions, and there were no dropouts.

Based on these results, we expect a high degree of compliance. Furthermore, in order to enable participants to follow the recommended protocol, they will be provided with written instructions on the protocol. Participants will also receive telephone calls periodically throughout the length of the trial, to reinforce their trial adherence.

All adverse effects observed will be recorded at each follow-up. If the researchers detect any incidental finding (e.g., a mass or lesion) at any time throughout the duration of the study, the participant will be informed and subsequently referred to the appropriate health professionals.

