### Randomization, blinding, and allocation

After baseline assessment, participants will be allocated randomly to each study arm. Off-site computer-assisted, centralized stratified block randomization will be conducted. Stratification will be conducted according to trial centers. Each participant will receive a sequentially numbered, sealed, opaque, and tamper-proof envelope from the trial coordinator at the respective center, containing the concealed allocated intervention. The trial coordinator will give each participant a demonstration as well as verbal and written instructions for following the protocol in their corresponding study arm.

This person will also serve as the contact person for the participants to discuss any issues regarding the study treatments throughout the duration of the trial. The research trainee and all other investigators involved in the study will be blinded to the intervention.

Because of the nature of the intervention, it is not possible to blind the participants. However, all appointments will be organized in such a way as to minimize communication between participants and to prevent potential study contamination. Additionally, participants will be requested to keep their group allocation confidential and not discuss it with the research team involved in the study analysis. The intervention will start the day after the study participants receive the opaque envelopes allocating them to one of the groups.

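### The only stated recording times for adverse effects are 3 and 6 months, but the pilot's fell in the first few days; the pilot's 40% also needs reconciling with a stated low frequency

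*Protocol article*

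**What the plan says.** The section on risks, participant safety and trial adherence sets the recording rule: "All adverse effects observed will be recorded at each follow-up". The Data collection section gives the dates: "Follow-up data collection will be conducted at 3 and 6 months post randomization by the same examiner at each research center". The abstract agrees on the two time points: "Participants will be assessed at baseline, and at 3 and 6 months post intervention".

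The risks section also reports what the pilot found: "mild pain and minor bleeding of the mucosa occurred in 40% of the 48 study participants in the first few days". It calls this discomfort minor and adds that everyone kept to the pilot's procedures and nobody dropped out. Exposure begins almost at once, according to the section on randomization, blinding and allocation: "The intervention will start the day after the study participants receive the opaque envelopes".

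Two contacts between visits are described. Periodic telephone calls are planned, with adherence as their stated purpose. The trial coordinator is available to participants who want to raise an issue about the study treatments. Neither is described as an occasion for recording adverse effects.

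The Statistical analysis section refers to the same pilot, with the same citation: "An interim analysis has not been planned due to the low frequency of adverse effects observed during the pilot trial".

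**The concern.** The stated recording times do not match the known timing of the harm. The one adverse effect that the protocol can already describe is early, mild and apparently short-lived. The first stated occasion for writing it down comes when most participants would have to remember something minor from about three months before.

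This matters because the trial is meant to support a practice guideline and to spare patients the harms of antifungal overtreatment. Weighing palatal brushing against alternatives needs a sound count of brushing's own main known harm, by randomized arm. If that count rests on recall, it may be incomplete.

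A second, smaller point is that the reason given for having no interim analysis describes the pilot's adverse effects in a way that the pilot figure elsewhere in the article does not support.

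**Working it through.** **Inputs**

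- Pilot rate: 40% of 48 (risks section).
- Pilot timing: the first few days (risks section).
- Start of brushing: the day after the envelope is received (randomization section).
- First stated recording: 3 months after randomization (Data collection, read with the risks section).
- Arm size: 26 (Sample size).

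**Step 1. Reproduce the pilot figure.** 18/48 = 37.5%, 19/48 = 39.6%, 20/48 = 41.7%. Only 19 rounds to 40%, so the figure means 19 participants.

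**Step 2. Its precision.** Exact (Clopper-Pearson) 95% interval for x = 19, n = 48:

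- lower limit = 2.5% quantile of Beta(x, n − x + 1) = Beta(19, 30) = 25.8%
- upper limit = 97.5% quantile of Beta(x + 1, n − x) = Beta(20, 29) = 54.7%

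Even the lower limit is about one participant in four.

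**Step 3. Expected number in the brushing arm.** 26 × 19/48 = 10.3, so about 10. If the pilot rate is taken as known, the central 95% binomial range for 26 participants is 6 to 15. If instead the interval limits are used as the rate, the expected number runs from 26 × 0.258 = 6.7 to 26 × 0.547 = 14.2.

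**Step 4. Gap to the first stated recording.** Three months is about 91 days. If the first few days are taken generously as the first week (an assumption), the gap is at least 91 − 7 = 84 days, or about 12 weeks.

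**Step 5. What cannot be computed.** The share of these events that would be forgotten or left unreported at 3 months is not given and cannot be derived from the document. The counts in Step 3 are events exposed to recall, not events lost.

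**Step 6. The two descriptions of the pilot side by side.** The risks section gives a frequency of 40%, with low severity. The Statistical analysis section says "due to the low frequency of adverse effects observed during the pilot trial" and does not mention severity. Both cite the same pilot. As a statement about frequency, the second does not agree with the first. As a statement about severity, it would agree.

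**The case against.** The strongest reply is that the recording rule names an occasion and excludes no other. The periodic calls and the coordinator could bring early events to light, and a visit record can cover everything since the previous visit, so a first-week event can still be reported at month 3. When the calls fall and what the caller asks are operational details that a journal article may leave to a fuller document. The effects are minor, and the pilot rate is already disclosed.

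Much of this stands. A reader might infer that recording at any other time is ruled out; the text does not say so. A reader might also infer that the trial will under-record these events and make brushing look safer than the pilot did. The document does not show that either: it gives no recall rate and does not say how the pilot collected its 40%.

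What remains is that the article does fix recording times, and the two it fixes are far from when its own data place the main known harm. The calls have a different stated purpose and no stated timing. The coordinator route depends on participants raising an issue, which could differ between arms. The data monitoring committee checks data that have been collected and entered, so it cannot recover events that were never recorded.

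On the pilot description, the mild effects and absence of dropouts make it plausible that low severity was meant. The sentence nevertheless says frequency and uses it to justify a design decision.

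**Conclusion.** The point holds in a limited form. The only stated recording times are 3 and 6 months, while the protocol's own pilot places adverse effects in the first few days. At the pilot rate about 10 of 26 brushing participants would be affected almost 3 months before the first stated recording, so capture would depend on recall and may be incomplete. This assumes that the pilot's rate and timing recur, that the pilot rate applies to people who brush, and that no earlier recording is arranged in a document not shown. The size of any loss is unknown.

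The low-frequency wording conflicts with the 40% and should be reconciled. A reader might infer from the conflict that an interim analysis is needed. It does not follow: the conflict is in the stated reason, the effects are described as minor, and no estimate, test or sample size changes.

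**What to change.** - Schedule one of the telephone calls already planned in the first week, at the same time in both arms.
- Have the trial coordinator ask a fixed adverse-effect question, including pain and bleeding, and record onset, duration and severity. The coordinator already knows the allocation, so the blinded examiners need not hear answers that could reveal it.
- State in the risks section that these reports count as adverse-effect records alongside those from the 3- and 6-month visits, and report them by arm.
- In the Statistical analysis section, reword the reason for having no interim analysis so that it agrees with the 40%, for example by giving low severity as the reason if that was meant.

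The cost is a short script, one form and a few minutes per participant. The drawback is that a subjective report is collected by someone who knows the allocation. An identical script in both arms reduces that risk of bias but does not remove it. The rewording costs nothing.
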